**A.3. Serum Total and Allergen-Specific IgE; Eosinophil count.** Total serum IgE will be measured from cord blood samples, and from year 1 and year 3 samples from the children. In addition, allergen-specific IgE and eosinophil counts will be measured from the year 3 samples from the children. Total IgE will be measured in the Channing Laboratory by the UniCAP 250 system (Phadia AB in Portage, MI ), with samples measured in duplicate. Serum from each child will also be assayed for IgE to 13 allergens (dust mite [*D. farinae*], cockroach [*Bla g*], cat dander, dog dander, rye grass pollen, ragweed pollen, *Alternaria tenuis*, *Aspergillus*, wheat, soybean, egg white, milk, and peanut) using the UniCAP system (Phadia AB in Portage, MI ). For specific IgE, the enzyme-immunoassay is based on the sandwich technique, utilizing a solid phase (allergen-impregnated discs) for separation. Sensitization to common allergens can be detected by measuring serum IgE specific to those allergens. We will define sensitization to each allergen as a specific IgE level  $\geq 0.35$  IU/ml. Atopy will then be defined as sensitization to at least one of the 13 allergens included in the study. Total serum IgE is increased in atopic individuals. For the statistical analysis, total serum IgE will be transformed to a log natural scale, in recognition of the distribution of total serum IgE in human populations. Total eosinophil counts will be determined at each clinical center's laboratory.

**A.4. Respiratory tract infections.** Lower respiratory tract infections (LRIs) will be defined based on parental responses to questionnaires. LRIs will be defined as a parental report of a physician's diagnosis of pneumonia, bronchiolitis, bronchitis, or croup (laryngotracheobronchitis).

**B. Screening Questionnaire.** This short questionnaire will be administered/obtained at the screening visit at the time of the first pre-natal visit to determine eligibility based on the presence or absence of asthma or allergies in the mother or in the biologic father of the child. If the subject or the biologic father has either asthma or allergies, then the Study Admissions Criteria Form that inquires about the other inclusion and exclusion criteria will be filled out.

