#### **P.2.a. Plan for *Specific Aim 1***

The hypothesis that the incidence of asthma and recurrent wheeze at age three years is reduced in the high-dose Vitamin D supplementation group will be tested using logistic regression, allowing for fixed effects of center. Additional analyses will consider the modification of vitamin D exposure effects by maternal and child demographic/behavioral factors such as maternal age, BMI and weight gain during pregnancy, maternal history of asthma/allergy, and other factors potentially associated with asthma and/or vitamin D exposure. The variables to be considered are summarized in Table 3. For variables that are measured post-natally, recall bias is a potential confounder among parents of infants diagnosed with asthma. However, the prospective nature of the data collection should limit the extent of this and other potential sources of bias. Due to the design of this clinical trial, we expect that the randomization process will distribute these variables equally between the intervention and control groups. However, we will check the distribution of these variables prior to conducting the analyses, and will adjust for variables that may be unevenly distributed across treatment and control groups.

**Table 3. Information on selected potential confounders of the relationship between 25(OH)D levels and asthma/recurrent wheeze in 3-yr old children**

|                                  |                                                                                 |
|----------------------------------|---------------------------------------------------------------------------------|
| Prenatal variables               | Socioeconomic status                                                            |
|                                  | Maternal diet                                                                   |
|                                  | Maternal sun exposure behavior                                                  |
|                                  | Maternal age and parity                                                         |
|                                  | Maternal history of asthma and allergies                                        |
|                                  | Maternal pre-pregnancy BMI and weight gain in pregnancy                         |
|                                  | Maternal medication use in pregnancy (antibiotics, acetaminophen, NSAIDs, etc.) |

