### P.3 Multiple comparisons.

All pre-specified hypotheses will be tested individually at the 0.05 level of significance, using a conservative two-sided alternative hypothesis (even when the stated hypothesis is one-sided). More specifically, the primary and secondary hypotheses of Vitamin D supplementation and Asthma/Recurrent Wheeze, Allergy/Eczema/LRI, will not be adjusted for multiple comparisons, since they have been defined a priori and are limited in scope. Additionally, an interim analysis plan has been developed for the primary outcome to adjust for the number of times (3) asthma and/or recurrent wheeze will be analyzed over the study period. Since 25(OH)D status is being examined in 5 separate analyses (maternal plasma at 26-28 weeks, maternal plasma at delivery, cord blood at delivery, infant plasma at years 1 and 3), this analysis will be adjusted for 5 multiple comparisons (i.e., using Bonferroni correction). Finally, any findings with respect to interaction terms (i.e., exploring whether environmental and demographic covariates affect the relationship between Vitamin D supplementation and the outcome of interest) for any of the hypotheses will be adjusted (i.e., using FDR methodology) for the number of models tested, and interaction testing will be limited to those defined in sections D.14.2a-c, in order to limit the potential for spurious findings. Any serendipitous findings coming from exploratory analyses will be clearly reported as such, and test statistic p-values will be adjusted by the number of exploratory hypotheses considered (using FDR or another appropriate procedure for multiple comparisons adjustment).

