## Q. Power and sample size

**Q.1. Power for Specific Aim 1.** The trial is designed to detect a 25% reduction in asthma and recurrent wheeze incidence at 3 years in the vitamin D supplemented (4400 IU) group. Based on the observational results in the Viva Study, we estimate that the incidence of asthma and/or recurrent wheeze in the standard dosing group (400 IU) will be 40-50%. This incidence estimate is based on observations from Project Viva and the URECA Project. **In project Viva, the prevalence of persistent wheeze is 44% and of asthma is 56.2% in children born to families with parental history of asthma (about twice the prevalence in children without family history).** These estimates are similar to those observed in the URECA Project in children who have turned 2 yrs old. The children in that cohort had a family history (mom or dad) of asthma or allergies. **In the URECA cohort, 99 of 194 (51.0%) children who have reached their 2nd birthday, have experienced "wheezing or asthma by age 2."** These observed rates in 2 cohorts give us confidence that we will see similar rates when we recruit the high-risk (for asthma and allergies in the child) pregnancies for this clinical trial. We anticipate an 8% miscarriage rate and 17-18% LTF among remaining subjects over the study period, resulting in an estimated sample size of 660 subjects (330 per arm) at the end of the study period. Each power estimate is based on 10,000 simulations. The simulations incorporate an interim analysis plan using the Lan-Demets spending function described in section VII.M, although the power may be slightly lower than the estimates presented here. For our group sequential design, we plan to use a Lan-Demets spending function with four approximately equally-spaced looks (with respect to the amount of information collected) and O'Brien-Fleming type bounds. The software program LANDEM (<http://www.biostat.wisc.edu/landemets/>) was used to calculate the stopping boundaries, which were  $|z|=4.3329, 2.9631, 2.3590$ , and  $2.0141$  at the first, second, third, and final looks, respectively. As noted in N.2.A.1, Lan-DeMets procedure provides a spending function approach which does not require pre-specification of the frequency or timing of interim looks. Therefore, the thresholds will be adjusted if the recruitment targets vary or if the need for more frequent monitoring arises. The hypothesis tests are conducted with two-sided alternatives (i.e. a two-sided p-value). The power reflects the proportion of replicates where the Wald test statistic from the hypothesis test of  $\beta_1=0$  is less than the stopping boundary specified for the first, second, or third looks, where  $\beta_1$  is the coefficient for Vitamin D supplementation status from the logistic regression model outlined in section N.2.a. The replication is considered a 'success' if the stopping boundary is exceeded at any of the analysis times. In the simulations, the incidence of asthma and/or recurrent wheeze at the first and second interim looks is proportionate to the overall incidence expected at the end of the study period (i.e. at the first look, the incidence is one-third of the specified rate; at the second look, it is two-thirds). We do not expect incidence rates of 40-50% to be achieved until the third year of follow-up; therefore, the simulations reflect the approximate amount of information anticipated at each interim analysis.

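### The primary logistic model adjusts for centre only; pre-specifying parental asthma would add a little power (near zero to about 3.5 points) and remove reliance on a data-driven imbalance rule

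*Supplement*

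**What the plan says.** - **Primary model (P.2.a).** The primary comparison "will be tested using logistic regression, allowing for fixed effects of center". The model equation contains arm and two centre indicators and nothing else.
- **Parental history in the design (Q.1).** Outcome frequencies in children with parental asthma are given from an outside cohort (persistent wheeze 44%, asthma 56.2%) and described as "about twice the prevalence in children without family history".
- **Who enters (section IV).** A pregnancy qualifies if either parent has asthma, eczema or allergic rhinitis. Some children therefore have a parent with asthma and others do not.
- **Collection (VI.B).** The screening questionnaire is used "to determine eligibility based on the presence or absence of asthma or allergies in the mother or in the biologic father of the child".
- **Where parental history appears in the analysis.** Table 3 lists "Maternal history of asthma and allergies" among potential confounders. P.2.a adjusts for variables found to be unevenly distributed, and the effect-modification model keeps significant main effects. Table 3 has no row for the father's history.
- **Randomisation (VII.C).** Strata are site and racial/ethnic group, so parental asthma is balanced only by chance.
- **Addendum to the Analysis Plan.** It brings in interval-censored time-to-event analysis and names no covariates.

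**The concern.** A baseline variable that predicts a binary outcome makes the treatment test more powerful when it is in the model. Here such a variable is known in advance, is fixed before randomisation and differs between participants, yet it is outside the primary model.

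The protocol follows the better principle elsewhere. For Specific Aim 4 (P.2.d), known determinants of 25(OH)D stay in the model whether or not they reach significance. The primary outcome has no matching rule.

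The fallback rules are also loose. P.2.a gives no threshold for an uneven distribution, so whether maternal history is adjusted for, and hence which estimate is reported as adjusted, is settled after the trial data have been seen. Some power and some clarity about the primary estimate are at stake. The type I error of the planned test is not.

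**Working it through.** **1. Inputs from the documents.** The significance rule is in P.3: "All pre-specified hypotheses will be tested individually at the 0.05 level of significance, using a conservative two-sided alternative hypothesis". The target effect is in Q.1: "The trial is designed to detect a 25% reduction in asthma and recurrent wheeze incidence at 3 years". Control incidence is 40-50%. The evaluable number is also in Q.1: "resulting in an estimated sample size of 660 subjects (330 per arm) at the end of the study period". This agrees with 870 × 0.92 × 0.82 = 656 and 870 × 0.92 × 0.83 = 664. Control incidence differs by 10 points across the three sites. The final boundary is |z| = 2.0141.

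**2. Reproducing the plan's power.** With the arcsine formula that Q.1 names, power = Φ(h·√(n/2) − 1.96), where h = 2·asin√p₁ − 2·asin√p₂ and n = 330. At 45% against 33.75%, h = 0.2308, h·√165 = 2.965, and Φ(1.005) = 0.843.

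| Control incidence | Table 4, 25% reduction | Arcsine | Two-proportion formula |
|---|---|---|---|
| 50% | 0.906 | 0.901 | 0.901 |
| 45% | 0.837 | 0.843 | 0.842 |
| 40% | 0.773 | 0.770 | 0.769 |

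All nine cells of Table 4 agree within 2 points. Table 4 is therefore right for the model without parental asthma.

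**3. Adding parental asthma.** The documents give neither the share π of children with parental asthma nor the within-trial risk ratio R, so both are assumed. Stratum risks in controls are p/(1 − π + πR) without parental asthma and R times that with it. For example, p = 45%, π = 50% and R = 2 give 30% and 60%. The treated arm has 75% of each risk. Sites are set at the mean −5, 0 and +5 points. In 4,000 simulated trials per scenario, the Wald test for treatment was compared between the arm + centre model and the same model plus one yes/no covariate for any parental asthma.

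Power without → with the covariate, π = 50%, |z| > 1.96:

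| R | Control 50% | Control 45% | Control 40% |
|---|---|---|---|
| 2.0 | 0.900 → 0.922 | 0.834 → 0.864 | 0.769 → 0.801 |
| 1.5 | 0.908 → 0.912 | 0.839 → 0.851 | 0.770 → 0.774 |
| 1.25 | 0.900 → 0.903 | 0.849 → 0.851 | 0.770 → 0.776 |

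Gain in points over all scenarios:

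| R (range of π) | \|z\| > 1.96 | \|z\| > 2.0141 |
|---|---|---|
| 2.0 (30-70%) | 1.4 to 3.4 | 1.5 to 3.9 |
| 1.5 (30-50%) | 0.4 to 1.2 | 0.1 to 1.4 |
| 1.25 (50%) | 0.2 to 0.7 | 0.4 to 0.5 |

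Monte Carlo error on each power is √(power(1 − power)/4000), about 0.5 to 0.7 points. Both models were fitted to the same simulated trials, so their difference is measured better than two separate runs would allow. Gains of a few tenths of a point are still close to nothing.

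**4. What a chance imbalance could do.** With π = 50%, the SD of the arm difference in parental asthma is √(2 × 0.25/330) = 3.9 points, so 2 SD is 7.8 points. At R = 2 (60% against 30%) this shifts the risk difference by about 0.078 × 30 = 2.3 points, against a designed difference of 0.25 × 45 = 11.25. At R = 1.25 the stratum risks are 50% and 40%, and the shift is about 0.078 × 10 = 0.8 points.

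**The case against.** **The two-fold figure does not describe this trial.** A reader might infer from Q.1 that parental asthma doubles the risk among these children. Q.1's comparator is children without family history, and eligibility excludes them. The contrast that matters is asthma against eczema or rhinitis only, and no figure is given for it. Q.1's second cohort, with a parental history of asthma or allergies, had 51.0%, which Q.1 calls similar. As a rough illustration, take 51% overall and 56.2% with parental asthma. If one third have parental asthma, the remaining risk is (51 − 56.2/3)/(2/3) = 48.4%, a ratio of 1.16. If two thirds have it, the remaining risk is 40.6%, a ratio of 1.38. Ages and outcomes differ, so this is only indicative, but it points below 2. This objection stands and is why the gain is given as a range.

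**Imbalance is already addressed.** P.2 will look for imbalance in important asthma risk factors, and P.2.a promises adjustment and mentions other factors beyond those it names. It would therefore go too far to say that paternal history can reach no analysis at all, or that imbalance is ignored. This stands in part: the routes exist, but they are data-driven, and P.2.a then refers the reader to Table 3, where the father is absent.

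**Paternal asthma may not be recorded separately.** One might infer that both parents' data are in hand. VI.B describes an eligibility check for asthma or allergies in either parent, and the baseline questionnaire (VI.C) asks for demographic details of the father. Separate recording is plausible but is not stated. This stands and makes part of the fix conditional.

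**The simulated model is not exactly the proposed one.** It has one covariate for either parent, whereas the fix has one for each. This stands; the power of the two-covariate model was not computed.

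**Arm plus centre is a legitimate primary analysis.** Agreed.

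**Conclusion.** The point holds as a modest improvement in efficiency and pre-specification. The primary model leaves out a baseline predictor that varies within the trial. Maternal history has only data-driven ways in, and paternal history is not in Table 3.

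The documents do not support reading this as a flaw in the test or in the power statement: the test is valid under randomisation and Table 4 reproduces.

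Power rose in every simulated scenario, by about 1.5 to 3.5 points if the within-trial risk ratio is 2.0 (extremes 1.4 and 3.9 over both critical values), by up to about 1.4 points at 1.5, and by under 1 point at 1.25. These figures rest on assumed shares and risk ratios, an equal relative reduction in both strata, a single binary covariate, and the final test alone without interim looks. The case for changing the plan rests as much on fixing the adjusted model beforehand as on the power gained.

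**What to change.** 1. Confirm that the screening forms record asthma separately from eczema and rhinitis for each parent, and that the father's items are completed when the mother already qualifies.
2. In P.2.a, name maternal asthma (yes/no) as a fixed covariate in the primary logistic model beside centre. If step 1 is confirmed, add paternal asthma (yes/no, with a stated category for unknown).
3. State that these variables are included whatever their balance or significance, so that the imbalance rule no longer decides on them.
4. Put the same covariates in the addendum's interval-censored time-to-event model.
5. Report the standardised risk difference and risk ratio beside the conditional odds ratio.

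**Cost.** A short edit to the plan, with no new visits or participants. The odds ratio becomes conditional on parental asthma and is not directly comparable with one adjusted for centre only, which the standardised risks address. Some paternal data may be missing, hence the stated category for unknown.

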where  $x_i$  denotes an indicator function for level of vitamin D supplementation (0=400 IU, 1=4400 IU) in the  $i^{\text{th}}$  subject, while  $a_{1,i}$  and  $a_{2,i}$  are indicator functions for study center. The specific aim for this outcome tests the hypothesis that  $\beta=0$ , asthma and recurrent wheeze incidence do not significantly differ across treatment groups, after adjusting for the potential effects of study center heterogeneity.

To assess modification of vitamin D exposure levels by other demographic and/or behavioral variables, the model is:

$$\text{logit Pr}(M_i = 1 \mid x_i, a_i) = \alpha + \beta x_i + \gamma_1 a_{1,i} + \gamma_2 a_{2,i} + \sum_k \delta_k z_{ki} + \sum_k \eta_k x_i z_{ki}$$

where  $z_{ki}$  represents the  $k$  measured covariates for each subject, and the other variables are as described above. This model addresses two hypotheses. First, main effects testing for behavioral/demographic covariates (Table 3), or the hypothesis that  $\delta_k=0$ , will be used to examine whether maternal age, BMI, or other factors predict asthma and recurrent wheeze risk at age 3. More importantly, inclusion of any significant main effects will adjust for any distributional imbalances of these factors across the Vitamin D supplemented and placebo

groups. Second, this model tests the hypothesis that  $\eta_k=0$ , or whether any maternal, child, or demographic/behavioral covariates modify the relationship between vitamin D intake and our primary outcome. To obtain a parsimonious model and limit multiple testing, only covariates with significant main effects and strong biologic plausibility for an exposure-dependent impact on asthma/recurrent wheeze risk will be considered for interaction testing with Vitamin D supplementation status. For example, only the prenatal and some delivery variables (e.g., gestational age, birthweight, length) listed in Table 3 will be considered, as the factors modifying the impact of Vitamin D supplementation on asthma and/or recurrent wheeze should occur temporally (i.e. in utero).

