where the parameters are as defined in Specific Aim 1. The  $k$  measured covariates for these analyses will be environmental, maternal, and child factors specific to 25(OH)D levels, such as sun exposure behavior, dietary intake of Vitamin D, and ethnicity. Additionally, any relevant covariates from Table 9 demonstrating main effects that have biologically plausible interactions with Vitamin D supplementation will be tested for effect modification. For both models, it is assumed that  $\varepsilon_i \sim N(0, \sigma^2)$ . The hypothesis that  $\delta_k=0$  will be used to examine whether any of these factors predict 25(OH)D levels, and the results will be used to adjust for any distributional imbalances of these factors across Vitamin D supplementation groups. As with the previous specific aims, we will also tests for effect modification via the hypothesis that  $\eta_k=0$ , or whether any maternal, child, or demographic/environmental covariates modify the relationship between vitamin D intake and circulating 25(OH)D levels in mother's plasma or cord blood. Additionally, we will follow the guidelines outlined in Specific Aim 2 to obtain the most parsimonious model.

The hypothesis that 25(OH)D levels in the child's blood will be higher in the 4400 IU group at birth, age 1 and age 3 will be tested using a repeated measures analysis framework such as generalized estimating equations.

#### P.2.d. Plan for Specific Aim 5

This specific aim investigates whether sufficient vitamin D supplementation in the pregnant mother is associated with reduced incidence of preterm birth (birth <37 weeks gestation) and/or preeclampsia, gestational hypertension, and/or HELLP syndrome compared to a usual care control group in VDAART.

The hypothesis that the incidence of preterm birth/preeclampsia, gestational hypertension and HELLP syndrome (PB/PE) is reduced in the high-dose vitamin D supplementation will be tested using logistic regression, allowing for fixed effect of center. Additional analysis will consider the modification of vitamin D exposure effects by maternal demographic/behavioral factors such as maternal age, BMI and weight gain during pregnancy, and maternal history of asthma/allergy, race, and other factors potentially associated with preterm birth/preeclampsia, gestational hypertension, HELLP or vitamin D exposure.

Letting  $M_i$  be an indicator function for the primary endpoint, PB/PE, for the  $i^{\text{th}}$  subject, the model is:

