$$\text{logit Pr}(M_i = 1 | x_i, a_i) = \alpha + \beta x_i + \gamma_1 a_{1,i} + \gamma_2 a_{2,i}$$

where  $x_i$  denotes an indicator function for level of vitamin D supplementation (0=400 IU, 1=4,400 IU) in the  $i^{\text{th}}$  subject, while  $a_{1,i}$  and  $a_{2,i}$  are indicator functions for study center. The specific aim for this outcome tests the hypothesis that  $\beta=0$ , PB/PE incidence do not significantly differ across treatment groups, after adjusting for the potential effects of study center heterogeneity.

To assess modification of vitamin D exposure levels by other demographic and/or behavioral variables, the model is:

$$\text{logit Pr}(M_i = 1 | x_i, a_i) = \alpha + \beta x_i + \gamma_1 a_{1,i} + \gamma_2 a_{2,i} + \sum_k \delta_k z_{ki} + \sum_k \eta_k x_i z_{ki}$$

where  $z_{ki}$  represents the  $k$  measured covariates for each subject, and the other variables are as described above. This model addresses two hypotheses. First, main effects testing for behavioral/demographic covariates, or the hypothesis that  $\delta_k=0$ , will be used to examine whether maternal age, BMI, or other factors predict PB/PE. More importantly, inclusion of any significant main effects will adjust for any distributional imbalances of these factors across the vitamin D supplemented and placebo groups. Second, this model tests the hypothesis that  $\eta_k=0$ , or whether any maternal, child or demographic/behavioral covariates modify the relationship between vitamin D intake and our primary outcomes. To obtain a parsimonious model and limit multiple testing, only covariates with significant main effects and strong biologic plausibility for an exposure-dependent impact on PB/PE risk will be considered for interaction testing with vitamin D supplementation status. **Because of our fixed sample size we have chosen to combine PB and PE as our primary outcome.** Obviously we would like to explore the disease entities separately, and also examine the effect of race independent of vitamin D level. These analyses can be done using interaction terms and stratified analyses recognizing that we have lower power to detect these influences.

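### The covariate main-effects test in P.2.a is placed in the model that already holds the treatment-by-covariate terms, so it tests the covariate in the 400 IU arm only, yet it decides which interactions are examined

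*Supplement*

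**What the plan says.** P.2.a (Plan for Specific Aim 1) gives two logistic models. The first has treatment and centre only, and the aim's hypothesis β = 0 is tested there. Treatment x "denotes an indicator function for level of vitamin D supplementation (0=400 IU, 1=4400 IU) in the" ith subject.

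The second model, introduced for effect modification, adds Σδ_k z_k and Ση_k x z_k together. Of this model the plan says: "This model addresses two hypotheses. First, main effects testing for behavioral/demographic covariates (Table 3), or the hypothesis that" δ_k = 0, to see whether maternal age, BMI or other factors predict the outcome. It goes on: "Second, this model tests the hypothesis that" η_k = 0. Both tests are thus assigned to the same equation.

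Two further statements depend on δ_k:

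- On imbalance: "inclusion of any significant main effects will adjust for any distributional imbalances of these factors across the Vitamin D supplemented and placebo" groups.
- On screening: "only covariates with significant main effects and strong biologic plausibility for an exposure-dependent impact on asthma/recurrent wheeze risk will be considered for interaction testing" with supplementation status.

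No covariate model without product terms is written, and centring of the covariates is not mentioned.

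Aim 5 repeats the logistic form ("First, main effects testing for behavioral/demographic covariates, or the hypothesis that" δ_k = 0). Aim 4 has the linear version and says "the results will be used to adjust for any distributional imbalances of these factors across Vitamin D supplementation groups". The Addendum to the Analysis Plan does not alter any of this.

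**The concern.** A main effect, as the plan uses the term, is the association of a covariate with wheeze across the trial. In a model with a 0/1 treatment indicator and a product term, the coefficient on the covariate alone is its association in the reference arm. A test of that coefficient draws essentially on half the children.

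The screening rule makes this matter. A covariate reaches interaction testing only if δ_k is significant. A factor that changes risk only under 4400 IU is a natural form of effect modification, but it has δ_k = 0 by construction and would normally be screened out. Ordinary predictors, with the same slope in both arms, are also missed more often than they should be. The list of reported predictors, the covariates kept for adjustment and the list of candidate modifiers would all rest on the wrong test.

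**Working it through.** **1. What δ_k means.** In the displayed model the log-odds are α + βx + centre + δ_k z_k + η_k x z_k. The slope of z_k is δ_k at x = 0 and δ_k + η_k at x = 1. So δ_k = 0 is a statement about the 400 IU arm alone. As a check, one simulated data set (no centre terms) gave δ = 0.06107 (SE 0.01973) in the interaction model. Fitting the 400 IU arm by itself gave the same estimate and SE.

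**2. The plan's own figure.** Table 4 gives power 0.906 for 50% against 37.5% with 330 per arm. The arcsine formula gives Φ(|2·asin√0.50 − 2·asin√0.375| × √(330/2) − 1.96) = Φ(0.2527 × 12.845 − 1.96) = Φ(1.286) = 0.901, which agrees. The sample size also follows: 870 × 0.92 × 0.825 = 660. This power belongs to the model with treatment and centre only, so the point here does not touch it.

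**3. Approximate power of the two covariate tests.** From the plan: 330 per arm, control incidence 45% (middle of 40–50%), 25% reduction, two-sided 0.05. Assumed, because the documents give no covariate figures: one covariate in SD units with log-odds slope b.

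- Binomial variances: 0.45 × 0.55 = 0.2475 in the 400 IU arm; 0.3375 × 0.6625 = 0.2236 in the 4400 IU arm.
- SE of the slope, main-effects model: 1/√(330 × 0.4711) = 0.0802.
- SE of δ_k, interaction model: 1/√(330 × 0.2475) = 0.1107.
- Power ≈ Φ(b/SE − 1.96).

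| Assumed common slope b per SD | Main-effects model | δ_k in displayed model |
|---|---|---|
| 0.15 | 46% | 27% |
| 0.20 | 70% | 44% |
| 0.23 | 82% | 55% |
| 0.30 | 96% | 77% |

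At b = 0.23 the pair is 80% and 54% with 40% control incidence, and 83% and 55% with 50%.

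**4. Simulation of the same setting** (4,000 trials per setting, three centres in the model):

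| Assumed truth | Main-effects model | δ_k in displayed model |
|---|---|---|
| No association | 5.3% | 4.7% |
| Slope 0.23 per SD in both arms | 80.9% | 52.6% |
| Slope 0.5 per SD in the 4400 IU arm only | 80.9% | 4.8% |

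The last row is what step 1 predicts: the true δ_k is zero, so the test rejects at its nominal 5%. The main-effects model sees an average slope of about 0.5 × 0.2236/0.4711 = 0.237.

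**5. A different assumed covariate** (mean 27, SD 6, slope 0.05 per unit, control incidence near 50%, treatment odds ratio 0.60; 1,500 trials) shows the same pattern. Power is 95.7% against 76.0% with a common slope. It is 43.8% against 3.9% when the slope exists only in the 4400 IU arm. Centring the covariate does not change δ_k.

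**The case against.** The best reply is that the plan describes a staged procedure. If only covariates with significant main effects go forward to interaction testing, main effects must be known before product terms enter. The displayed equation is then a general template, and under that reading the fault disappears. This has force, and it may be what was intended. But the first-stage model is nowhere written, and the text expressly gives δ_k = 0 to the equation containing the product terms. An analyst following the words would fit the wrong test.

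Three stronger readings are tempting, and the documents do not support them.

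- **That the imbalance-adjusted treatment effect is read from β of the interaction model.** That β is the effect at z_k = 0. With uncentred age (assumed mean 27, SD 5.5) its SE grows by √(1 + (27/5.5)²) = 5.0, and simulated power is 9% against 83%. But no passage names this β as a reported estimate. P.2.a promises adjustment for uneven variables separately, without giving a model, and is silent on centring. The figure holds only if that β were used uncentred.
- **That the test is wrong for every covariate.** P.2.a limits interaction candidates to prenatal and some delivery variables. Postpartum covariates in Table 3 would carry no product term. In Aim 4, sun exposure, diet and ethnicity stay in whatever δ_k shows.
- **That Aim 3 inherits the model.** P.2.c refers to the Aim 2 plan, which in the current version has no such model.

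It is also fair to say that these are additional analyses, with FDR control on the interactions, and that δ_k keeps its nominal size when there is no association.

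**Conclusion.** The point stands for the covariate test. As written in P.2.a, and in the same form for Aims 4 and 5, δ_k = 0 is a 400 IU-arm test for any covariate with a product term, and it is used as a gate to interaction testing. That conclusion is algebra and needs no assumption.

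The size does depend on assumptions, since the documents give no covariate distributions or slopes. With 330 per arm and 45% control incidence, a predictor found with about 81% power by a proper main-effects test is found with about 53%. A covariate acting only in the 4400 IU arm at 0.5 per SD is found about 5% of the time against 81%. The loss shrinks for strong predictors.

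The primary test of β in the centre-adjusted model, and Table 4, are untouched. The plan leaves open which model supplies an imbalance-adjusted treatment effect. That is a gap to close, not a demonstrated error.

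**What to change.** In P.2.a, and in the parallel text for Aims 4 and 5, write two covariate models.

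1. **Main-effects model:** treatment + centre + Σδ_k z_k, with no product terms. Test δ_k here, and state as a safeguard that any imbalance-adjusted treatment effect comes from this model.
2. **Interaction model:** add the x z_k terms for covariates that pass the screen, with continuous z_k centred at the overall mean. Use it only to test η_k.

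The change is to wording. It needs no new data, visits or software. It is not wholly neutral: a different screen may admit a different set of covariates, so the set of η_k tests and the number entering the FDR correction in P.3 may change. The text should be settled before anyone sees which covariates pass.
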